### 2.3. Inclusion Criteria

Patients will be eligible if they meet the following criteria:(1)Diagnosed with ONFH at Tohoku University Hospital(2)Stage 1–3B and Type B–C2 according to the Japanese classification(3)Age ≥ 18 years(4)Provided written informed consent(5)Surgery can be performed within 18 months after the initial diagnosis or worsening of symptoms.

No upper age limit is specified because the study aims to reflect real-world clinical practice. Most enrolled patients are expected to be relatively young to middle-aged adults, consistent with the epidemiology of ONFH.

### 2.4. Exclusion Criteria

Patients will be excluded if they:(1)Have a history of hip surgery(2)Are pregnant or breastfeeding(3)Have ONFH secondary to trauma, tumor, or other specific diseases. Patients with steroid-induced or alcohol-related ONFH will be included because these etiologies represent common forms of non-traumatic ONFH.(4)Have contraindications to artificial bone materials.

### 2.5. Intervention

All surgical procedures will be performed under general anesthesia using a traction table. First, hip arthroscopy will be conducted to assess intra-articular pathology, including acetabular cartilage, femoral head cartilage, and labral integrity. If a labral tear is identified, appropriate repair will be performed. Subsequently, core decompression will be performed under fluoroscopic guidance. A guidewire will be inserted into the necrotic lesion to confirm correct positioning. Core decompression will be performed using a cylindrical bone biopsy instrument. Next, OCP/Gel (Bricta^®^, Nipro, Osaka, Japan) will be transplanted into the necrotic cavity. OCP/Gel, which received regulatory approval in Japan in May 2024 and has been covered by national health insurance since October 2024, was used as the graft material in this study. The volume of graft material will be determined intraoperatively according to the extent of the lesion and the size of the cavity created during core decompression. Formal volumetric assessment is not planned in this pilot study. Because the graft material is radiolucent, intraoperative assessment of graft filling will be performed based on the insertion depth and position of the delivery instrument, as well as arthroscopic visualization. Finally, the joint will be inspected arthroscopically to confirm the absence of graft leakage. All procedures will be performed by experienced orthopedic surgeons familiar with hip arthroscopy and joint-preserving procedures for ONFH.

### 2.6. Evaluation Methods

**Primary outcome**

The primary outcome will be progression of ONFH within 1 year from baseline. Progression will be defined as the occurrence of either of the following events: (1) radiographic stage progression according to the classification system of the Japanese Investigation Committee of Idiopathic Osteonecrosis of the Femoral Head, or (2) conversion to total hip arthroplasty (THA). Baseline will be defined as the time of surgery in the intervention group and the time of initial diagnosis based on radiographic findings at Tohoku University Hospital in the historical control group. Radiographic stage progression will be assessed using anteroposterior radiographs obtained preoperatively and at 1 year. Collapse will be quantified by measuring the collapse length (mm), defined as the distance between the femoral head contour and a best-fit spherical outline on the femoral head. Radiographic evaluations, including assessment of disease progression and collapse length, will be performed independently by two orthopedic surgeons. Any discrepancies will be resolved by consensus. Because complete blinding to clinical information is difficult in this study, formal blinded assessment is not planned. In addition, formal assessment of interobserver agreement is not planned because of the exploratory nature of this pilot study.

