## 1. Introduction

Osteonecrosis of the femoral head (ONFH) is a common hip disorder characterized by femoral head collapse, which can lead to secondary osteoarthritis, resulting in severe hip pain and functional limitations [1]. In most cases, intraosseous necrosis has already occurred at the time of diagnosis, making early detection difficult, and patients are often asymptomatic before femoral head collapse, with spontaneous reduction in the necrotic area being rare and larger lesions more likely to progress to collapse [1,2]. A national epidemiological survey conducted in 2004 estimated that approximately 11,400 patients with ONFH were treated annually in Japan, with approximately 2200 new cases diagnosed each year [3]. Once femoral head collapse occurs, patients develop pain and gait disturbance, ultimately leading to irreversible deterioration of hip joint function, and many patients with ONFH require surgical treatment, with more than half undergoing surgery within nine months of diagnosis [4]. Total hip arthroplasty (THA) is indicated in advanced stages with substantial joint destruction and provides excellent pain relief and functional outcomes; however, complications such as infection and dislocation can occur, and long-term mechanical loosening may necessitate revision surgery [1,5,6]. Moreover, several studies have suggested that patients with ONFH may experience higher complication and revision rates after THA compared with those with primary osteoarthritis [7,8,9]. Because ONFH often affects relatively younger patients, the indication for THA should be considered carefully, and joint-preserving procedures are preferred before substantial joint destruction occurs [5,10]. Femoral osteotomy procedures, such as transtrochanteric rotational osteotomy and curved varus osteotomy, have been widely performed in Japan to transfer the viable portion of the femoral head to the weight-bearing area while shifting the necrotic region away from load-bearing zones [11,12]. However, these procedures are highly invasive, involving substantial disruption to bone, musculotendinous structures, and the joint capsule, and their utilization has shown a decreasing trend based on a Japanese nationwide database study [13].

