### 2.2. Population

We will include 25 patients with ONFH. As an external control, historical data will be extracted from patients previously diagnosed with ONFH and treated conservatively at Tohoku University Hospital. Eligible patients in the historical cohort must meet the following criteria: (1) diagnosis of ONFH based on radiographic and MRI findings at the time of initial presentation; (2) classification as Stage 1, 2, 3A, or 3B (excluding Stage 4) and Type B, C1, or C2 according to the criteria of the Japanese Investigation Committee (JIC) of Idiopathic Osteonecrosis of the Femoral Head [40]; (3) age ≥ 18 years at the time of diagnosis; and (4) no restriction on sex [41]. Eligible patients in the historical cohort will be selected to match the study population as closely as possible. Historical control data will be extracted from patients treated conservatively at Tohoku University Hospital between Jun 2005 and May 2021. During this period, radiographic and MRI-based diagnosis and staging were performed according to the Japanese Investigation Committee classification. Nevertheless, temporal changes in clinical practice and patient management may have influenced the outcomes and should be considered when interpreting the results.

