## 3. Discussion

This study aims to evaluate the efficacy and safety of arthroscopy-assisted core decompression combined with OCP/Gel implantation for osteonecrosis of the femoral head (ONFH). This combined approach integrates mechanical support, biological regeneration, and intra-articular assessment, representing a minimally invasive joint-preserving strategy. This approach may be particularly beneficial in patients with pre-collapse or early-stage ONFH, especially in those with medium-to-large necrotic lesions at risk of collapse.

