This study has several strengths. It evaluates a novel combined technique that addresses both intraosseous and intra-articular pathology. In addition, the externally controlled design with propensity score matching allows for adjustment of baseline differences between groups, improving the validity of comparisons. Furthermore, both radiographic and clinical outcomes are assessed, enabling a comprehensive evaluation of treatment effectiveness. However, several limitations should be acknowledged. First, this is a single-center study with a relatively small sample size, as this trial was designed as a pilot study, which may limit generalizability. Second, the use of a historical control group introduces potential selection bias and residual confounding, despite statistical adjustment. In particular, differences in treatment indications and clinical practice over time may have influenced the outcomes. Baseline is defined as the time of surgery in the intervention group and the time of initial diagnosis in the historical control group. This asymmetry may introduce bias because disease progression occurring before surgery in the intervention group is not captured. Furthermore, residual confounding due to unmeasured factors, including corticosteroid use, alcohol consumption, symptom duration, and temporal changes in clinical practice, cannot be completely excluded. In addition, baseline patient-reported outcome measures, including the HHS and JHEQ, are not available for the historical control cohort. Therefore, these outcomes will be evaluated descriptively within the intervention group, and direct comparisons between groups will not be possible. Third, the follow-up period is limited to short-term outcomes, and long-term durability, including prevention of femoral head collapse and conversion to total hip arthroplasty, remains unclear. In addition, the collapse length measurement used in this study has not been formally validated, and intra- and inter-observer reliability were not assessed. Therefore, measurement variability may influence the reproducibility of radiographic outcomes. Finally, variability in surgical technique and patient characteristics may influence the results. Therefore, caution is required when generalizing the findings to other populations and clinical settings. In conclusion, this study is expected to provide important preliminary evidence regarding the feasibility and potential effectiveness of arthroscopy-assisted core decompression combined with OCP/Gel implantation. The findings may contribute to the development of improved joint-preserving strategies for ONFH and support future large-scale prospective studies. This approach may offer a practical and scalable alternative to more complex regenerative therapies.

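### The primary composite counts any THA within a year as disease progression, so THA at an unchanged stage can create a group difference without any effect on the disease

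*Protocol article*

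**What the plan says.** Section 2.6 of the protocol article sets the endpoint: "The primary outcome will be progression of ONFH within 1 year from baseline". An event is a Japanese Investigation Committee stage change "or (2) conversion to total hip arthroplasty (THA"). For this endpoint, "Radiographic stage progression will be assessed using anteroposterior radiographs obtained preoperatively and at 1 year". The section asks for no stage change before a THA counts. It also says that formal blinded assessment is not planned.

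Time zero is surgery in the intervention group and initial diagnosis in the controls. The Discussion calls the intervention one "representing a minimally invasive joint-preserving strategy". For the controls, Section 2.2 says that "historical data will be extracted from patients previously diagnosed with ONFH and treated conservatively at Tohoku University Hospital", "between Jun 2005 and May 2021".

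Three other places bear on the point:
- The secondary outcomes in Section 2.6 include radiographic progression at 3, 6 and 12 months on the same classification. Table 1 schedules X-rays for trial patients at every follow-up visit and at discontinuation.
- Section 2.10 matches on baseline covariates, tests the primary outcome with McNemar's test and handles missing data by complete-case analysis.
- The Discussion concedes that "differences in treatment indications and clinical practice over time may have influenced the outcomes", and notes the different time zeros. It ties neither remark to the THA component.

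**The concern.** Stage progression is read from the hip. THA is something clinicians and patients choose, and the Introduction itself says that its indication needs careful thought in younger patients. In the treated group, year 1 opens with an operation meant to preserve the joint. In the controls it opens at diagnosis, under conservative care. Whoever considers THA knows which situation applies, so the same pain at the same stage may lead to THA in one group and to further observation in the other. Only the first is counted as progression.

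Matching on age, sex, body mass index, stage, type and etiology balances the groups at baseline. It cannot equalise a decision taken afterwards.

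The stated aim is to promote bone regeneration and prevent collapse, and Section 2.10 says that the estimates will be used to size later trials. A difference in readiness to offer THA, reported as a difference in disease progression, would mislead on both counts.

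**Working it through.** **Inputs.** The plan states no event rate, THA rate, effect size or power, so there is no figure of its own to reproduce. From the documents come at most 25 matched pairs (25 patients, 1:1 matching), McNemar's test and two-sided 0.05. The following are assumptions:
- r, the stage-progression rate, equal in both groups (no effect on the disease);
- qC and qT, the proportions of hips without stage progression that have THA within the year, in controls and treated hips.

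**Which THAs matter.** A THA after a stage change adds nothing, because that hip is already an event. Only THA at an unchanged stage moves the composite. It is possible in this population: Stage 3B hips are eligible, and a 3B hip can be replaced before any change to Stage 4 is recorded.

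**Formula.** Composite rate = r + (1 − r) × q.

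**Size of the spurious difference, r = 0.30.**
- Controls, qC = 0.10: 0.30 + 0.70 × 0.10 = 0.37.
- Controls, qC = 0.20: 0.30 + 0.70 × 0.20 = 0.44.
- Treated, qT = 0: 0.30.
- Treated, qT = 0.02: 0.30 + 0.70 × 0.02 = 0.314.
- Smallest difference: 0.37 − 0.314 = 0.056. Largest: 0.44 − 0.30 = 0.14.

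**Chance of a significant result favouring the intervention** (25 independent pairs, r = 0.30, qT = 0, McNemar's test by exact enumeration):

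| qC | Composite, control vs treated | Exact test | Uncorrected chi-square |
|---|---|---|---|
| 0 | 30% vs 30% | 1.1% | 2.1% |
| 0.10 | 37% vs 30% | 4.0% | 6.4% |
| 0.20 | 44% vs 30% | 10.4% | 15.3% |

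With 15 pairs and qC = 0.20 the chances are 5.2% and 10.4%. Losing pairs lowers the chance of significance but leaves the 14-point bias in the estimate unchanged.

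**The other direction.** With qC = 0 and qT = 0.10 the composite is 30% in controls and 37% in treated hips, a bias of 7 points against the intervention. This is not fanciful. If selecting controls as conservatively treated leaves out patients operated on early, control THA is too low by construction. Section 2.2 does not settle this.

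**Does the secondary radiographic outcome act as a check?** A hip replaced at, say, month 8 has no native 12-month film. The composite keeps it as an event. In the 12-month radiographic outcome it has no value, and complete-case analysis could delete it. The hips that separate the two readings are thus the ones at risk of being lost.

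**The case against.** The strongest objection is that much of the remedy is already in the plan. Radiographic progression alone is a secondary outcome, and Section 2.10 has secondary outcomes compared between groups. In treated patients the scheduled films mean that a hip replaced mid-year will usually have been staged beforehand. A reader of the primary-outcome paragraph alone might infer that stage is read only before surgery and at 1 year, so that the plan cannot tell the two kinds of THA apart. That is true of the primary endpoint but not of the plan. What stands is narrower: no rule covers hips replaced before 12 months, and nothing connects the radiographic outcome to the reading of the composite.

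Two other strong readings also fail:
- The Introduction describes patients needing surgical treatment, "with more than half undergoing surgery within nine months of diagnosis". A reader might take this as a THA rate for the controls. It covers any surgery in ONFH generally, including osteotomy, whereas the controls were chosen as conservatively treated.
- A reader might infer that the bias must favour the intervention. That is the likelier direction, but the documents give no THA rates, do not say who decides on THA, and leave open whether controls with early surgery are kept.

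The Introduction also says that THA is indicated in advanced stages with substantial joint destruction. THA at an unchanged stage may therefore be uncommon, at least in pre-collapse hips, and the 10–20% assumed above may be too high.

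Finally, counting THA as failure keeps replaced hips in the analysis. That is a good reason to retain the composite, not a reason to leave its parts unseparated.

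**Conclusion.** The point holds in limited form. As defined, the composite can differ between groups through THA at an unchanged stage alone, and the planned secondary radiographic outcome does not reliably reveal this. Under the declared assumptions the spurious difference is 5.6 to 14 points. With 25 pairs, 20% of stage-stable controls replaced and no treated hips replaced, the chance of a false significant benefit rises from 1.1% to 10.4% on the exact test. These figures show the mechanism and do not forecast this trial. The true size is unknown. The direction probably favours the intervention, but could reverse through control selection. For a pilot whose estimates feed later trials, this is worth correcting before the data are read.

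**What to change.** Keep the composite as the primary outcome and add the following:
- **Classify each THA.** In both groups, read the stage on the last available native-hip film before THA. Report how many converted hips have no such film, especially among the historical controls.
- **Name a supporting analysis of the primary outcome.** Use stage progression alone, from the 1-year film or the last pre-THA film, in place of complete-case deletion of replaced hips.
- **Report by group:** stage progression, THA after stage progression, and THA without it.
- **Limit the claim.** State slowed progression or prevented collapse only if the radiographic component points the same way. If the difference comes from THA at an unchanged stage, report it as a difference in THA use.
- **State the control rule.** Say whether conservatively treated patients who had THA or other surgery within the year stay in the control pool, since the direction of bias depends on it.

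The cost is protocol wording and a small number of extra readings by the two planned readers. The radiographic analysis will have fewer events, and the headline effect may be smaller. Table 1 covers only the prospective patients, so interim films in the controls may be incomplete. A hip replaced at an unchanged stage might also have progressed later in the year. The last-film analysis counts it as not progressed and the composite counts it as progressed, so the two should be shown together.

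### The one-year primary outcome starts at surgery in the treated group but at diagnosis in the controls; the protocol admits the asymmetry and plans no remedy

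*Protocol article*

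**What the plan says.** All references are to the protocol article.

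- **Endpoint (2.6, Primary outcome).** "The primary outcome will be progression of ONFH within 1 year from baseline". Either a rise in radiographic stage or conversion to THA counts.
- **Time zero (2.6).** "Baseline will be defined as the time of surgery in the intervention group and the time of initial diagnosis based on radiographic findings". For controls this means the diagnosis made at the study hospital.
- **Films (2.6).** "Radiographic stage progression will be assessed using anteroposterior radiographs obtained preoperatively and at 1 year". The treated hip's starting stage is therefore its stage at surgery.
- **Delay (2.3, criterion 5).** "Surgery can be performed within 18 months after the initial diagnosis or worsening of symptoms". Because the clock may run from worsening, the interval from diagnosis can exceed 18 months.
- **Entry.** A treated hip must be "Stage 1–3B and Type B–C2 according to the Japanese classification" (2.3). A patient is excluded for the criterion "Have a history of hip surgery" (2.4).
- **Adjustment (2.10).** Matching is 1:1 on a propensity score built from age, sex, body mass index, stage, type and etiology. Time since diagnosis is not in it. Year of diagnosis is collected but left out.
- **Acknowledgement (3. Discussion).** "This asymmetry may introduce bias because disease progression occurring before surgery in the intervention group is not captured". Symptom duration is also listed there as a source of residual confounding. No analysis is attached to either statement.

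**The concern.** A treated hip can pass through a period after diagnosis that is not counted, while its matched control is counted from the first day. The two groups are then compared over different stretches of the disease, and treated hips must still have been eligible when their stretch began. If risk of progression changes with time since diagnosis, or if patients come to surgery for reasons linked to that risk, one-year progression differs between groups even when the operation does nothing. Matching on stage does not cure this, because it can pair a hip well after diagnosis with one at first diagnosis of the same stage.

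This affects the main result. The primary outcome is tested at two-sided 0.05 with McNemar's test, and section 2.10 says the progression rates and effect size will inform the sample size of later confirmatory studies.

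**Working it through.** The protocol gives no progression rates, no delay distribution and no effect size, so it has no figure to reproduce. The check has two parts.

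**1. How the same event is treated in each group**

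| Event soon after diagnosis | Treated group, if before surgery | Control group, if within 1 year |
|---|---|---|
| Reaches Stage 4 | Cannot enter | Counts as progression |
| THA | Cannot enter | Counts as progression |
| Stage rises within 1–3B | Enters at the new stage; not counted | Counts as progression |

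**2. Size under no treatment effect (illustration)**

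Assumptions, none of them from the protocol:
- Stage moves occur at rate Zλ per year, where Z is a gamma frailty with mean 1 and variance θ.
- One-year progression from diagnosis is 50%, so (1 + θλ)^(−1/θ) = 0.5. With θ = 1, λ = 1.
- The number of moves k to Stage 4 is 4 from Stage 1, 3 from Stage 2, 2 from Stage 3A and 1 from Stage 3B. A hip can enter at delay s (years) if it has made fewer than k moves. THA from earlier stages is ignored.
- Starting mixes over Stages 1, 2, 3A, 3B: early 40/30/20/10%, even 25% each, late 10/20/30/40%.

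Formulas for θ = 1:
- P(n moves by s) = [1/(1+s)] × [s/(1+s)]^n
- P(no move in the next year, given n) = [(1+s)/(2+s)]^(n+1)

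At s = 1.5:

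| n | P(n) | P(no move, given n) | Product |
|---|---|---|---|
| 0 | 0.4000 | 0.714 | 0.2857 |
| 1 | 0.2400 | 0.510 | 0.1224 |
| 2 | 0.1440 | 0.364 | 0.0525 |
| 3 | 0.0864 | 0.260 | 0.0225 |

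Summing over n < k gives the one-year risk among hips that can enter:
- From Stage 3B (k = 1): 1 − 0.2857/0.4000 = 28.6%
- From Stage 3A (k = 2): 1 − 0.4082/0.6400 = 36.2%
- From Stage 2 (k = 3): 1 − 0.4606/0.7840 = 41.2%
- From Stage 1 (k = 4): 1 − 0.4831/0.8704 = 44.5%

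Even mix: the entry total is 0.4000 + 0.6400 + 0.7840 + 0.8704 = 2.6944, and the no-move total is 0.2857 + 0.4082 + 0.4606 + 0.4831 = 1.6376. The risk is 1 − 1.6376/2.6944 = 39.2%, against 50% in controls. The spurious benefit is 10.8 points.

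The same calculation for the other cases (points of spurious benefit, θ = 1):

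| Delay | Early mix | Even mix | Late mix |
|---|---|---|---|
| All at 6 months | 2.2 | 3.5 | 4.9 |
| All at 18 months | 8.8 | 10.8 | 13.3 |
| Uniform 0–18 months | 3.7 | 5.0 | 6.5 |

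Uniform delays with other variances: 1.8 to 3.4 points at θ = 0.5 and 7.8 to 11.8 points at θ = 2, so about 2–12 points overall. With a constant hazard that is the same for every hip, the bias is zero.

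**The opposite direction.** Suppose half of control hips are fast progressors (90% one-year risk) and half slow (10%): 0.5 × 0.9 + 0.5 × 0.1 = 50%. If worsening brings patients to surgery and 65% of treated hips are fast, their risk is 0.65 × 0.9 + 0.35 × 0.1 = 62%. At 80% fast it is 74%. An operation without effect would then look harmful by 12 or 24 points.

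**The case against.** **It is disclosed, and this is a pilot.** Both are true, so this is an acknowledged limitation and not an oversight. Disclosure does not let a reader correct the estimate, however, and the pilot's stated purpose is to supply that estimate.

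**The bias may be small or absent.** This stands. Eighteen months is a limit, not a typical delay. If surgery follows diagnosis closely, or the hazard is constant and homogeneous, little or nothing remains.

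**A reader might infer that treated hips are progression-free survivors.** Conditioning on no event before surgery gives one-year risks of 40%, 33% and 29% at 6, 12 and 18 months, hence a spurious benefit of 10 to 21 points. The entry criteria do not support that reading: a hip that moved from Stage 1 to 2, or from 2 to 3A, still qualifies. Those figures apply only to hips starting at Stage 3B (the k = 1 case). Leaving out THA from earlier stages does make the smaller figures somewhat low.

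**A reader might also take the controls as newly diagnosed disease.** Their baseline is diagnosis at the study hospital, so earlier diagnosis elsewhere is not excluded.

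**Re-indexing may not be feasible.** Section 2.10 says that routine imaging records exist. It does not say that controls have interim films at usable dates, and the pool size is not given. Adding a covariate also strains a model the authors already wish to keep small. Alignment must therefore depend on what the films allow.

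**Conclusion.** The point holds. As written, the primary comparison uses unequal time zeros, excludes from one group events that count in the other, and has no analysis that addresses this. The contrast and the planning effect size can be biased.

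The protocol does not let us state the direction. Selection of still-eligible hips favours the intervention if risk falls with time since diagnosis; surgery prompted by worsening can work against it. It would therefore be wrong to say that the plan is bound to show a false benefit.

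Under the stated assumptions (50% one-year progression, frailty variance 1, only Stage 4 excluded, varied starting stages), the spurious benefit is about 4–6 points for uniform delays and 9–13 points if all delays are 18 months. Over variances 0.5 to 2 with uniform delays it is about 2–12 points. These figures illustrate the mechanism and are not predictions for this trial.

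**What to change.** 1. Record time from diagnosis to surgery for every treated patient and report its distribution.
2. Where control films allow, index each candidate control at a film taken at a similar time since diagnosis, when the hip is still conservatively managed, Stage 1–3B, Type B–C2 and without THA. Take stage and type from that film, count the year from it, and match on time since diagnosis.
3. If films are too sparse for this to be the primary analysis, prespecify it as a sensitivity analysis, together with one limited to patients operated on soon after diagnosis. In that case, do not present the unaligned contrast as an estimate of treatment effect.

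The cost is analysis wording and the extraction of film dates from hospital records; treatment is unchanged. The downside is that controls without a film near the matched time drop out, by a number the protocol does not let us estimate.
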